#### Intervention adherence

The intervention is a behavioral intervention that requires the surgeon to remember and implement a new behavior pattern; thus, adherence needs to be assessed. Adherence to the StOP?-protocol will be measured for each operation. Adherence is assessed using a standardized reporting form filled in by each scrub technician present during the operation before they leave the operating room. They report if and how many StOP?s were performed during their presence and provide a simple quality rating of the StOP?s on a Likert scale from 1 (very bad) to 5 (very good); a definition of the characteristics of a good StOP? is provided (i.e., spoken loudly enough, complete (StOP? acronym), engaged, the complete team stopped working and paid attention). Adherence of reporting by the scrub technicians will be calculated by comparing the number of operations performed with the number of reports submitted. Adherence to the StOP?-protocol will be calculated by comparing the adherence reports of the scrub technicians for surgeons in the intervention group with the number of operations performed by these surgeons.

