#### Statistical methods for additional analyses

As a secondary analysis, we will perform a per-protocol analysis, excluding operations where the surgeon in the intervention group did not adhere to the protocol and where surgeons in the control group actually performed a StOP?. However, it is now well known that a naïve per-protocol analysis is problematic as it does not properly take confounding/selection bias into account [42]. Direct and indirect adjustment methods are described to estimate the per-protocol effect of a point intervention such as the StOP?-protocol [43]. We will explore the possibility to directly adjust for confounders by using inverse probability weighting [43].

Because cluster randomization may lack the optimal balancing in characteristics between the groups seen in individual-level randomization, we will adjust each model for additional pre-defined patient-level, surgeon-level, and hospital-level variables to account for case-mix differences between the groups in a sensitivity analysis. Moreover, we will qualitatively assess the imbalances of hospital, surgeon, and patient characteristics between the groups. If we observe relevant imbalances in covariates not considered in the primary and sensitivity analyses, we will perform additional adjustments and consider propensity score-based approaches to assess the robustness of our results.

In exploratory analyses, we will assess the adherence and study the influence of the number of StOP?-protocols on outcomes. Such analyses include the assessment of the impact of surgeons’ gender or patients’ gender on primary or secondary endpoints.

We plan exploratory analyses based on the collected data. One such analysis concerns predictors of adherence to the protocol, based on adherence data. We also plan to investigate the changes in outcomes based on surgeon experience with the StOP?-protocol (number of operations with StOP?. Further exploratory analyses will assess the impact of surgeon and patient gender on adherence and on endpoints.

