*Interaction between the treatment and the control group*: An important aspect is that surgeons in the control group may be operating together with surgeons in the intervention group within a surgical department. Three different combinations are expected: (i) both surgeons are from the intervention group (25% of interactions), (ii) both surgeons are from the control group (25% of interactions), and (iii) one surgeon is from the intervention group and the other from the control group (50% of interactions). The observations from the StOP? I study showed that collaborations between board-certified surgeons are much more common in university (90% of the procedures) and large teaching (30% of procedures) hospitals, and less frequent in rural hospitals (5% of the procedures). We take this into account for the sample size calculation and the data analyses.

We will conduct exploratory analyses for operations jointly performed by surgeons that are assigned to different treatment groups with a special emphasis on the influence of hierarchical status on adherence to the StOP?-protocol.

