#### Analysis of population and missing data

The main analysis will be based on the intention-to-treat analysis set where all operations of a randomized surgeon done during the enrolment period are analyzed in the randomized arm, regardless of adherence. The per-protocol analysis set consists of all operations where the surgeon was adherent, i.e., if a surgeon in the control group performs a StOP?-protocol during an operation, such operations will be excluded and, if a surgeon in the intervention group does not perform a StOP?-protocol, such operations will be excluded.

We do expect only few missing data with respect to the primary outcome (30-day mortality). We will impute missing outcome data based on all available baseline characteristics of hospitals, surgeons, and patients using chained equations. Analyses will be conducted as described above using Rubin’s rules to combine measures across multiple data sets [44]. This will be done for the analyses of the primary endpoint and the three key secondary endpoints.

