If a surgeon from the intervention group collaborates with a control group surgeon, we define that during the collaborative phase, the surgeon with a higher hierarchical status acts according to his or her study condition. Thus, an intervention group surgeon with lower hierarchical status will not have to initiate StOP?s in the presence of a control-group surgeon with a higher hierarchical status.

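### The adherence rate and the per-protocol control exclusion are not reconciled with the rule that the higher-ranking surgeon's arm governs mixed-arm operations

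*Protocol article*

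**What the plan says.** **Conduct.** Under Risk-benefit assessment, the protocol article states that in a mixed-arm collaboration "the surgeon with a higher hierarchical status acts according to his or her study condition" while the two work together. It adds that "an intervention group surgeon with lower hierarchical status will not have to initiate StOP?s in the presence of a control-group surgeon" of higher status.

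**Adherence.** Under Intervention adherence, the scrub technicians fill in a form for each operation: "They report if and how many StOP?s were performed during their presence". The adherence rate is then obtained by "comparing the adherence reports of the scrub technicians for surgeons in the intervention group with the number of operations performed by these surgeons". No operations are exempted from that denominator. The Intervention section has adherence assessed at least monthly and the result returned to each surgeon, with support offered where adherence is a problem.

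**Per-protocol set.** Under Analysis of population and missing data, "if a surgeon in the intervention group does not perform a StOP?-protocol, such operations will be excluded". On the control side, "if a surgeon in the control group performs a StOP?-protocol during an operation, such operations will be excluded". Statistical methods for additional analyses uses the same control-side trigger: operations are excluded "where surgeons in the control group actually performed a StOP".

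**Frequency.** The same section reports from the earlier study that "collaborations between board-certified surgeons are much more common in university (90% of the procedures"), against 30% in large teaching and 5% in rural hospitals. It expects half of all such collaborations to be mixed-arm.

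**The concern.** The conduct rule creates two kinds of operation that the analysis definitions do not recognise.

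- **Junior intervention surgeon with senior control surgeon.** No StOP? is required. The operation still sits in the adherence denominator, so behaviour that the protocol permits reads as non-adherence in the rate, in the monthly feedback and in the planned search for predictors of adherence.
- **Junior control surgeon with senior intervention surgeon.** A StOP? is held, but the control surgeon does not perform it. If the operation is counted under the control surgeon, the exclusion is not triggered and an exposed operation stays among the per-protocol controls.

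The two sides are also treated unequally. The junior's senior-led mixed operation leaves the intervention side and stays on the control side. The inverse probability weighting that the article proposes to explore deals with confounding. It does not correct an exposed operation kept as unexposed.

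At stake are the readability of the adherence rate and a dilution of the per-protocol contrast towards no effect.

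**Working it through.** **Plan's own figure.** The sample size section states 84% power for 200 clusters per arm, mean size 24, coefficient of variation 0.5, ICC 0.024, and 1.8% versus 0.9% mortality. With design effect 1 + ((1 + 0.5²) × 24 − 1) × 0.024 = 1.696, the power is 83.5%. With a relative-efficiency correction for unequal cluster sizes (design effect 1.648) it is 84.5%. The stated figure reproduces, so its inputs are used below.

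**Share of mixed operations.**
- The target cluster size is raised from 24 to 30 to accommodate patients operated on by surgeons from different arms. The implied allowance is 1 − 24/30 = 20% mixed, that is, 40% joint operations at 50% mixed. The article does not state this percentage; it is read from the two cluster sizes.
- From the stated collaboration rates, mixed share = 0.5 × joint share: university 0.5 × 90% = 45%, large teaching 0.5 × 30% = 15%, rural 0.5 × 5% = 2.5%.

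**Share governed by the other arm's surgeon, x.** Assume that the senior surgeon comes from either arm equally often (randomization is 1:1, stratified by department and seniority) and that the rule covers the whole operation. Then x = mixed share / 2, in each arm.

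**Effect on the adherence rate.** If 60% of the operations in which a StOP? was required had one (the approximate rate in the earlier study), the reported rate is 0.6 × (1 − x).

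**Effect on the per-protocol odds ratio.** Assume that all of x on the control side receives a StOP?, is counted under the control surgeon and stays in the control set. Apply the planning risks to all operations alike. Control risk = 0.018 × (1 − x) + 0.009 × x, compared with 0.9%. Without such operations the odds ratio is (0.009/0.991)/(0.018/0.982) = 0.495.

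| Setting | Mixed | x | Reported adherence if 60% of required | Per-protocol odds ratio |
|---|---|---|---|---|
| Implied allowance | 20% | 10% | 54% | 0.522 |
| University | 45% | 22.5% | 46.5% | 0.559 |
| Large teaching | 15% | 7.5% | 55.5% | 0.515 |
| Rural | 2.5% | 1.25% | 59.3% | 0.499 |

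Worked line for x = 10%: control risk = 0.0162 + 0.0009 = 0.0171, and the odds ratio is (0.009/0.991)/(0.0171/0.9829) = 0.522.

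If senior intervention surgeons hold a StOP? in only 60% of these operations, the exposed control share in university hospitals is 0.6 × 22.5% = 13.5% and the odds ratio is 0.53.

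**The case against.** **Attribution.** The hypotheses concern use by the main surgeon. If a mixed operation were counted only under its senior surgeon, as the main surgeon, neither problem would arise. This is the strongest point, but the article gives no such rule. Its intention-to-treat set takes all operations of a randomized surgeon, under which a mixed operation could fall in both arms. The control-side problem is therefore conditional on attribution, and the missing rule is part of what needs fixing.

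**Mixed operations may be set aside.** Raising the cluster size from 24 to 30 can be read as not relying on them. The article enlarges the clusters but never says that these operations are removed from any set.

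**The form cannot tell who led.** As described, it records whether StOP?s occurred. In practice a control operation with any StOP? might then be flagged and dropped. That would be the sensible outcome, but it is not the written exclusion.

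**The topic is not ignored.** The article promises to take these interactions into account, and it plans exploratory analyses of mixed operations with emphasis on hierarchy and adherence. That stands, and a reader should not infer that the protocol overlooks mixed operations. Neither statement changes the two definitions. Because those definitions are written out, the conflict is between stated rules and is not a detail left to an analysis plan.

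**Dropping unexposed intervention operations is correct.** This also stands. An intervention operation without a StOP? does not belong in a per-protocol intervention group. The faults are the non-adherent label and the unequal treatment of the control side.

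**Conclusion.** The conflict is real and modest. Followed as written, the definitions count exempt operations as non-adherent and can keep StOP?-exposed operations among the per-protocol controls. At the implied 20% allowance about 10% of each arm is affected, and the per-protocol odds ratio moves from 0.495 to about 0.52. The range is 1.25% of operations in rural hospitals (odds ratio about 0.50) to 22.5% in university hospitals (about 0.56).

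These figures lean high. They assume an even seniority split, a rule that covers the whole operation, every board-certified collaborator enrolled although participation is voluntary, and mixed operations counted under the junior surgeon.

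Two stronger readings are not supported:

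- **A hard ceiling on adherence.** One might infer that measured adherence cannot exceed 1 − 22.5% = 77.5% in university hospitals, or 1 − 45% = 55% for juniors always paired with a senior. The rule only releases the junior from a duty and applies only during the collaborative phase. The article states neither the seniority split nor constant pairing.
- **Damage to the primary result.** The primary intention-to-treat analysis disregards adherence and does not use either definition. The effect is confined to adherence reporting and secondary analyses.

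**What to change.** Reconcile Intervention adherence, Statistical methods for additional analyses and Analysis of population and missing data with the hierarchy rule. The analysis definitions can be changed without touching the conduct rule.

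1. Exclude from the per-protocol control set any operation for which the scrub form records a StOP?, whoever led it.
2. State the arm to which a mixed-arm operation is attributed.
3. Report adherence twice: over all operations of intervention surgeons, which keeps overall uptake visible, and without the hierarchy-exempt operations. Show the exempt operations as a separate category, in the monthly feedback as well.

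The change is mainly one of wording. Surgeon IDs per operation, hierarchy level, and scrub forms for surgeons in both arms are already planned. The costs are a somewhat smaller per-protocol control set, mostly in university hospitals, and an imperfect exemption flag: it can be derived from surgeon IDs and hierarchy level, but the listed data do not show how long the collaborative phase lasted.

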The steering committee meets at least biweekly via videoconferencing. An agenda is sent at least a day beforehand and a protocol is written and distributed for each meeting by an administrator ([name]). The steering committee is also responsible for the study in the coordinating center.

## Discussion

### Interventions that aim at changing behavior are notoriously difficult to implement

Problems of adherence to a protocol have been reported for the introduction of checklists [21] as well as for the implementation of training [26]. Often, such interventions are perceived as additional load (e.g., by interrupting routines), requiring additional time and implying behaviors perceived as awkward (e.g., introducing oneself to a familiar team). Adherence may be difficult to achieve even if participants acknowledge the usefulness of the procedure in principle but get frustrated by a suboptimal implementation process [47].

### The StOP?-protocol is no exception

We invested quite some effort in ensuring adherence during the previous study [31]. This included information to all team members and interviews with most surgeons above the resident level to ensure their collaboration. We also collected adherence data after each operation during the intervention period and provided monthly feedback about adherence. In addition, the StOP?-protocol was strongly supported by all department heads of the participating hospitals. All this resulted in an adherence rate of approximately 60%. Thus, there is room for improvement, although it should be added that our adherence rate was similar to those at the beginning of the WHO checklist introduction [48]; higher rates may be achieved only after an intervention has become widely implemented and accepted, as now seems to be the case for the surgical checklist [48]. Efforts in ensuring adherence will be a major focus of the project.

### Threat of bias of contamination

Given that the study aims to change the behavior of surgeons in the treatment group, potential bias or contamination of the surgeons enrolled in the control group needs to be addressed: First, although surgeons in the control group do not receive training, they will not be blind to the intervention, as surgeons within a department work closely together. This could be a source of contamination, because surgeons in the control group may observe StOP?s performed while they operate with a surgeon in the intervention group. If control group surgeons observe communication behavior that they judge as promising, they may be motivated to copy this behavior. However, sporadic observations of others’ behaviors are not sufficient to sustainably change a behavior. Training and feedbacks would be necessary for sustainable behavioral changes.

Second, some participating hospitals may have implemented a sign-out, which partially overlaps with a StOP?. For surgeons in the intervention group, the training interview will address this and ask the surgeons to reflect to what extent a StOP? may be associated to the sign-out, so that both can be combined during the operation.

## Trial status

The protocol version V1.2, 4.2.2022 was approved by the Lead Ethics Committee 14.3.2022. Recruitment of surgeons in the first participating center is planned for August 2022. Date of recruitment completed: October 2025.

## Dissemination of study results

The results of this study will be important for four key audiences, namely:

A:Healthcare professionalsB:AcademiaC:Patients and the publicD:Policy makers and medical societies

If the study shows the expected results, the findings are of high importance and will be broadly received. Research is most effectively disseminated using multiple channels, adapted to the audiences.

During the study, we will build and maintain a network between participating study centers in order to exchange information, but also to provide regular feedback on the progress of the study. This will mostly be done using electronic means, but also regular videoconferencing and meetings. This network will also be used for the discussion and interpretation of the results (audiences A, B).

A webpage will be set up that allows communication with the study centers but also allows regular dissemination of information to an interested audience of healthcare professionals, media, and lay people (A, B, C, D). Via this webpage, webinars will be performed at least annually (A, B, C, D).

The results of the study will be published in peer-reviewed medical scientific journals and presented at national and international conferences (A, B, D). Newsletters will be sent by email (A, B, C, D). Mailing lists will be made available by the participating surgical societies and the two included patient organizations. After the study, toolkits of training materials will be offered free of charge (A). We will work closely with the media to inform the general public about the results of the study (A, B, C, D). Differences in outcome dependent on the gender of the surgeon as well as of the patient will be analyzed. The results of this analysis will be published (A, B, C, D)

## Reproducibility

We will deposit the final protocol in a preprint repository (medRxiv.org) and submit it to a peer-reviewed journal. At publication of the primary results, the full protocol, the data management plan including the codebook of the trial database, and information on how to get access to the primary trial data will be published in the repository of the University of Bern which fulfills the FAIR criteria (Bern Open Repository and Information System (boris.unibe.ch)). A 12-month grace period after publication of the primary results is currently foreseen to allow all collaborators to complete additional, pre-planned analyses and projects.

## Data Availability

Data will be deposited in the Bern Open Repository and Information System Research Data (BORIS-RD). BORIS-RD allows searching and is indexed by search engines. All items are stored with a unique Digital Object Identifier (DOI) that can be referenced in respective publications. It should be noted that we plan to register and deposit data that relates to individual, primary publications and not the whole study database as such. This enables other researchers to replicate published analyses and results as well as to re-use the data for additional analyses such as meta-analysis.

## Abbreviations

CI: Confidence interval
CONSORT: Consolidated Standards of Reporting Trials
ICC: Intracluster correlation coefficient
ITT: Intention-to-treat
SSI: Surgical site infection
WHO: World Health Organization
